Based on the consecutive recruitment of the open cohort, we plan to establish a temporal validation by using the same population at different times [15]. After a six-month and one-year follow-up, we will reanalyze sets of PROs-CP measurement tools to reaffirm the psychometric properties of the particular scale for people living with chronic pruritus over time. Cross-validity and reliability will be analyzed in order to establish the scale’s psychometric properties using an anchor-based questionnaire approach. Scale dimensionality for each multidimensional measurement tool will be reaffirmed using the confirmatory factor analysis (CFA) and non-parametric IRT methods. A quantitative method via face-to-face or video call using Zoom will also be employed. A random subsample (estimated approximately 50 patients) based on a one-on-one approach will be asked using structured and unstructured in-depth interviews to provide their perspectives on the face and content validity and relevancy of the PROs-CP tools. Moreover, based on feedback from patients and research personnel, the acceptability of scale measurement will be assessed through the study, along with the reasons for the unacceptability or unfavorable use of the PROs-CP measure in clinical practice.

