### Sample size estimation

Although we plan to include all eligible patients in this open longitudinal study, a pre-specified sample size for scale development and validation of the PRO-CP measurement tool was estimated. As such, sample size consideration for this study will be calculated based on two parameters. Firstly, we use a sample-to-item ratio (5–15 patients per question for both the EFA and CFA approach) to address a scale structure for factor analysis [8, 28, 29]. Secondly, a fair correlation coefficient statistic (>0.30) with anchor-based questions was used to establish convergent validity [34]. Regarding a power of 80% and 0.05 type I error, a minimum target of 396 patients with chronic pruritus is needed for this study cohort to account for missing responses of 20% during the cohort follow-up.

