### Statistical analysis plan

All statistical analyses will be analyzed using Stata, version 16.0 (StataCorp, College Station, Texas). The significant level was tested at *P* value <0.05 based on hypotheses of two-tailed tests. Missing values will be handled with a multiple imputation method. Descriptive statistics will be analyzed and presented as number (%), mean (SD), or median (min–max) as appropriate.

Item analysis will be assessed descriptively and summarized along with the normality of score distribution, including skewness and kurtosis tests. The Kaiser-Meyer-Olkin measure and Bartlett test of sphericity will be tested to ensure the appropriate scale factor analysis of the measurement scales. For preplanned EFA, we will employ a principle factor extraction method, with the obliquely rotated using the Promax criterion. Eigenvalues with a criterion of >1.0 will be considered as the number of factors retained. The unidimensional set or subscales will be tested using a non-parametric IRT. The item characteristics curve analysis will be visualized to describe the characteristics of individual items within the particular scale. During the follow-up period, we will perform a CFA with a maximum likelihood estimation to reaffirm the scale structure. Specific fit indices will be tested, including the comparative-fit index (>0.900), non-normed fit index or Tucker-Lewis index (<0.900), standardized root mean squared residual (<0.100), and root mean square error of approximation (<0.100).

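### The fixed CFA fit limits do not by themselves show how many dimensions a scale has; fit rival models and report the factor correlations

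*Protocol article*

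**What the plan says.** Under Study I, the Protocol article plans a re-analysis after six months and one year: "Scale dimensionality for each multidimensional measurement tool will be reaffirmed using the confirmatory factor analysis (CFA) and non-parametric IRT methods". The Statistical analysis plan section adds that "we will perform a CFA with a maximum likelihood estimation to reaffirm the scale structure". The criteria that follow are "comparative-fit index (>0.900), non-normed fit index or Tucker-Lewis index (<0.900"), then "standardized root mean squared residual (<0.100), and root mean square error of approximation (<0.100"). The list is open, since it begins "Specific fit indices will be tested, including the comparative-fit index (>0.900").

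Two other steps bear on dimensionality. The earlier exploratory analysis (EFA) uses principal factor extraction with Promax rotation, and "Eigenvalues with a criterion of >1.0 will be considered as the number of factors retained". Also, "The unidimensional set or subscales will be tested using a non-parametric IRT". The sample size section sets "5–15 patients per question for both the EFA and CFA approach", with a target of 396 patients that allows for 20% missing responses.

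The article names no competing CFA model, no nested comparison and no criterion for the correlation between factors.

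**The concern.** Each limit asks whether one model reproduces the observed correlations well enough. None asks whether a simpler or a richer model would do as well or better.

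- **Too many factors.** A model that subdivides the true factors contains the true model as a special case, with some factor correlations equal to 1. It passes whenever the true model passes, so passing does not show that the extra factors exist.
- **Too few factors.** With limits as wide as 0.90 and 0.10, a single factor can pass when two strongly related factors are present.

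Validating these instruments is the first primary objective, and Table 2 describes two of the new scales as multidimensional. If the number of dimensions is wrong, subscales may be reported that carry the same information twice, or two related constructs may be scored as one.

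**Working it through.** The fit limits are conventions, so the plan has no figure of its own to reproduce. The check is whether they separate right from wrong structures.

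**Inputs.** From the article: the four limits, ML estimation, eigenvalue >1.0, and n = 396 × 0.8 ≈ 317. Assumed: 10–20 items (Table 2 gives 17 for PUSH-D and 20 for TAS-20; item counts for the new scales are not given), loadings mostly 0.6 or 0.7, and continuous normal items. The Tucker-Lewis index (TLI) is read as >0.900 unless stated.

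**1. The TLI sign.** Higher TLI means better fit, so the printed direction conflicts with the other three limits. Applied literally with 20 items at loading 0.7, correctly specified two-factor models pass all four limits in 0% of samples.

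**2. One true factor, split.** With 12 or 18 items (loadings 0.6 or 0.7), arbitrary splits into 2 or 3 factors passed in 100% of samples. With 20 items (loadings 0.5 or 0.7), 2- and 4-factor models also passed in 100%. The estimated factor correlation was about 1.00. At loading 0.7 the 1-, 2- and 4-factor models had almost the same fit (CFI 0.997, RMSEA 0.010).

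**3. Two true factors, fitted as one.** Averages for 20 items at loading 0.7:

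| Factor correlation | CFI | TLI | SRMR | RMSEA | Passes |
|---|---|---|---|---|---|
| 0.8 | 0.922 | 0.913 | 0.053 | 0.066 | 78% |
| 0.7 | 0.860 | 0.843 | 0.075 | 0.087 | 3% |
| 0.5 | 0.723 | 0.690 | 0.120 | 0.121 | 0% |

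At 0.9 it passed in 100%. Across 10–20 items and loadings 0.6 and 0.7, the pass rate was roughly 70–97% at correlation 0.8, 0–35% at 0.7 and 0–4% at 0.6. At 0.7 the average SRMR and RMSEA are still inside 0.100, so CFI and TLI do the rejecting.

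**4. Does the EFA catch this?** For two equal blocks of p/2 items with loading λ and factor correlation φ, the second eigenvalue of the common part is (p/2)·λ²·(1−φ). At φ = 0.8:

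- p=20, λ=0.7: 10 × 0.49 × 0.2 = 0.98
- p=18, λ=0.7: 9 × 0.49 × 0.2 = 0.88
- p=12, λ=0.7: 6 × 0.49 × 0.2 = 0.59
- p=20, λ=0.6: 10 × 0.36 × 0.2 = 0.72

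All are below 1.0, so the rule tends to keep one factor. In simulation it did so in 100% of samples with 10–12 items, 81–100% with 18 and 48–96% with 20. EFA and CFA agreed on the wrong single factor in roughly half of samples (20 items, loading 0.7) up to 97%.

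For one true factor the second eigenvalue is 0. Its largest simulated value was 0.41, so EFA proposed a second factor in 0% of samples at loadings 0.6 and 0.7. Taking eigenvalues from the unreduced matrix gave at most 4%.

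**5. Does non-parametric IRT catch it?** Each half of a one-factor scale is itself unidimensional. Scalability was equal for halves and whole (0.34 and 0.34; 0.46 and 0.46), so testing within subscales cannot show redundancy. For two factors at 0.8 wrongly pooled, all samples met the usual 0.3 item limit (an assumption; the article gives none) at loading 0.7. At loading 0.6 the pooled scale usually failed, so IRT helps there.

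**6. Would a comparison catch it?** Take p=20, λ=0.7, φ=0.8. There are 20 × 21 / 2 = 210 moments. One factor uses 40 parameters (df 170) and two use 41 (df 169). From RMSEA² × df × (n−1):

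- One factor: 0.066² × 170 × 316 ≈ 234, so χ² ≈ 404.
- Two factors: 0.008² × 169 × 316 ≈ 3, so χ² ≈ 172.
- Difference ≈ 232 on 1 df, against a 5% critical value of 3.84.

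The difference test was significant in every simulated two-factor sample at correlation 0.8.

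**The case against.** Much of the case on the other side stands, and it limits the point.

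- **A reader might infer that any over-split structure passes.** It does not. Four-factor splits cutting across two true factors passed in 3% of samples at correlation 0.7 and 0% at 0.5 or below. Over-splits of a one-factor scale with residual covariances of 0.2–0.3 passed in 0–3% (though the one-factor model then passed in 0% too). Only splits that subdivide the true factors are bound to pass, and only when the true model itself fits.
- **A reader might infer that absolute fit limits alone decide the matter, or that the CFA can show nothing about dimensions.** CFI and TLI are incremental indices, the list is open, and non-parametric IRT is planned alongside. The CFA does reject one factor in most samples at a correlation of 0.7 and almost always at 0.6 or below.
- **The 100% figure starts from a split that the planned EFA would almost never propose.** This is correct for loadings of 0.6–0.7. The over-splitting risk therefore lies mainly with structures taken from theory or from a published version.
- **A reader might infer that redundant subscale scores will enter Study III.** No section says that subscale scores are used there.
- **Rival models may be in a fuller plan, which a condensed article can leave out.** That is possible and lowers confidence. It does not change what the printed limits can show, and the EFA screen does not cover the under-splitting error.
- **At a correlation of 0.8, scoring one dimension or two is partly a judgement.** This is true, but the judgement needs the correlation and the rival fit in view.

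**Conclusion.** The point holds as a limit on what the stated criteria can show. With the TLI sign corrected, the four cut-offs are a reasonable minimum condition, but they do not by themselves establish how many dimensions a scale has.

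Over-splitting passes in 100% of samples when the split subdivides the true factors, but the planned EFA rarely creates it. Under-splitting is likelier under the planned sequence: at a factor correlation of about 0.8 a single factor passes in roughly 70–97% of samples, and EFA often points to the same answer. At 0.7 or below the limits mostly reject it.

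The sizes rest on n=317, 10–20 continuous normal items, equal loadings of mostly 0.6–0.7 and equal blocks. Real Likert items, unequal loadings or a different analysis sample would move them. This is a cheap improvement to the plan. It does not mean that the planned CFA is uninformative.

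**What to change.** For each multidimensional scale, fit three models to the same data: one factor, the EFA-derived structure, and the a priori structure (intended domains for the new scales, the published structure for the translated ones). Compare nested models by chi-square difference and others by BIC. Report every inter-factor correlation with its 95% CI. Claim separate subscales only when the multi-factor model fits better and the correlations are clearly below 1. Both conditions are needed, because a difference test this powerful can favour a split of little practical use.

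Keep the four cut-offs as a minimum condition, with TLI changed to >0.900.

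The cost is one or two extra models per scale, with no new data. Some subscales may be merged or split as a result. The article reports 70 patients enrolled and the new scales still at item generation, so the rule can be fixed before the CFA is run.

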### Study population

Based on routine clinical practice and to create an open or dynamic cohort, all adult patients with chronic pruritus, regardless of the IFSI classification to skin manifestation (i.e., inflamed skin, non-inflamed skin, and chronic secondary scratch lesions) in outpatient settings, will be consecutively recruited for this study project. Chronic pruritus patients will be diagnosed based on the recommendation of the IFSI—defined as pruritus lasting six or more weeks [1, 2]. Details of the eligible patients for the study are provided in Table 1.

**Table 1 pone.0314548.t001:** Eligibility criteria of the PROs-CP study.

Inclusion Criteria	Exclusion Criteria
• Patients aged ≥20 years at the date of screening • Diagnosed with chronic pruritus based on the IFSI recommendation, itch lasting more than 6 weeks [1, 2] • Could read and communicate in the Thai language • Had an ability to understand and willingness to sign an informed consent statement and adhere to the study protocol	• Inability to answer questions or comply with the study protocol due to both physical and mental disability • Recent hospitalization within 3 months • The prognosis for survival <12 months

Abbreviations: IFSI, International Forum for the Study of Itch; PROs-CP, Patients-Reported Outcomes among People Living with Chronic Pruritus.

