**Aspect of mental health, psychosocial, and psychosomatic symptoms**			
PHQ-9	Yes	Yes	• The PHQ-9 consists of 9 items to measure depressive symptoms (total score ranges from 0 to 27). • This scale showed excellent psychometric properties, with a Cronbach’s α of 0.90 among the general population in Thailand [29, 47]. • A cut-off point ≥9 was considered to indicate depressive symptoms [48].
GAD-7	Yes	Yes	• The GAD-7 consists of 7 items to measure anxiety symptoms (total score ranges from 0 to 21). • This scale had excellent psychometric properties, with a Cronbach’s α of 0.90 among the general population in Thailand [29, 47]. • A cut-off point ≥8 was considered to indicate depressive symptoms [49].
WHO-5 well-being index	Yes	Yes	• The WHO-5 well-being index consists of 5 items to measure health-related personal well-being. • This scale had excellent psychometric properties, with a Cronbach’s α of 0.91 among the general population in Thailand [29, 47]. • A cut-off point <50 was considered a low well-being index [47].
BRCS	Yes	Yes	• The BRCS consists of 4 items to measure cope tendencies with psychological stress (total score ranges from 4 to 20). • This scale had excellent psychometric properties, with a Cronbach’s α of 0.84 among the general population in Thailand [29].
TAS-20	Yes	No: translated and psychometric testing through this study	• The TAS-20 consists of 20 items to measure alexithymia (difficulty in identifying and describing emotions) [27]. • The non-Thai version showed adequate psychometric properties in 30 different languages (or dialects of the same language) [26].
PUSH-D	Yes	No: translated and psychometric testing through this study	• The PUSH-D is a dermatologic-specific scale to evaluate stigmatization in patients with visible skin conditions, which consists of 17 items [16]. • This scale demonstrated excellent psychometric properties, with Cronbach’s α 0.94 [16].
RSES	Yes	Yes	• The RSES consists of 10 items to measure self-esteem and is widely used in social science research. • The revised Thai RSES scale demonstrated excellent psychometric properties, with Cronbach’s α ranging from 0.84 to 0.86 [50].
UCLA Loneliness Scale-6	Yes	Yes	• The short version of the UCLA loneliness scale consists of 6 items to gauge loneliness levels. • This scale revealed acceptable psychometric properties in both non-clinical and clinical settings, with Cronbach’s α ranging from 0.72 to 0.84 [51].

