Two independent bilingual native English speakers will independently blind-translate the synthesized measurement scales back into English. For the back-translation process, no translators had any medical health/dermatology background or acknowledged information regarding the particular original English version. To ensure that the translated version reflects the content of the original version, the content validity of the back-translation questionnaire will be reviewed and addressed. After that, both versions of the backward translations will be compared and reconciled with the original English version. To ensure equivalence between the original and translated Thai versions, conceptual equivalence (ensuring that words can hold the same conceptual meaning), item equivalence (individual items have the same relevance), and semantic equivalence (meaning of the items is the same in both version) will be employed. In the same manner as pilot testing and refinement of the scale development, a panel of experts and patients will review and refine the preliminary translated scales. Next, the EFA, non-parametric IRT, and initially psychometric analysis will be conducted to establish the validity, reliability, and scale stability (reproducibility) of the translated scales Thai version (i.e., ItchyQoL, PUSH-D, and TAS-20).

To track the treatment responses, the responsiveness of the pruritus-specific disease activity control (planned to develop through this study) and pruritus-specific HRQoL (using the ItchyQoL) in terms of the MCID will also be defined and established among patients with chronic pruritus. For scale interpretability in terms of MCID, we will incorporate both anchor-based and distributional criterion approaches using the change scales of disease activity and ItchyQoL at week 12 of follow-up [31–33].

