To assess the psychometric properties, we will test the convergent validity of the sets of PROs-CP measurement scales using Pearson’s or Spearman’s correlation coefficients as appropriate. The 95% confidence intervals (CIs) of correlation coefficient statistics will be estimated using the bootstrap resampling method. A know-group or discriminant validity will be assessed based on pruritus intensity—visual analog scale as follows: mild (0.1–2.9), moderate (3.0–6.9), severe (7.0–8.9), and very severe (9.0–10.0) [2]. Internal consistency reliability will be tested using Cronbach’s α and McDonald’s ω coefficients with 95% CIs (values of >0.7 indicate acceptable reliability). Scale reproducibility will be tested using intraclass correlation coefficients. The kappa (κ) coefficient of the agreement and area under the receiver operating characteristic curve will be used to assess the optimal cut-off severity or burden score to establish banding of measurement scales with anchor-based questions.

All interviews’ audio recordings will be transcribed verbatim. Deidentified transcript data from the in-depth interview process will be uploaded, coded, and refined by professional experts in qualitative research (RA, CP, and YR). For qualitative analysis, we will employ content analysis to summarize the interview information and assess the consistency of coding and refinement concepts that capture patient views and experiences of chronic pruritus. A thematic approach based on grounded theory techniques will be used to analyze and identify patterns or themes (subthemes) from patient perspective information [35, 36]. Furthermore, we also plan to qualitatively synthesize among subgroups with severe or very severe pruritus intensity to reflect the impacts of chronic pruritus that are most important to patients with high-burden disease activity. The saturation of concept findings from qualitative interviews will be reaffirmed using saturation tables to verify and track the concepts of how pruritus affected the patient’s life.

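### Itch-VAS bands are the only known-group criterion named for the PROs-CP scales, and they are weak evidence either way for the Thai PUSH-D, a stigma scale for visible skin conditions

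*Protocol article*

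**What the plan says.** The psychometric paragraph of the Statistical analysis plan opens with the whole instrument set: "we will test the convergent validity of the sets of PROs-CP measurement scales". It then gives one known-group rule: "A know-group or discriminant validity will be assessed based on pruritus intensity—visual analog scale", with bands of 0.1–2.9 (mild), 3.0–6.9 (moderate), 7.0–8.9 (severe) and 9.0–10.0 (very severe). No scale is excepted, no other known group is named, and nothing restricts the comparison by skin manifestation.

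The Thai PUSH-D is one of the scales to be validated. Study I plans factor analysis, item response theory and initial psychometric analysis "to establish the validity, reliability, and scale stability (reproducibility) of the translated scales Thai version (i.e., ItchyQoL, PUSH-D, and TAS-20". Table 2 describes its target: "The PUSH-D is a dermatologic-specific scale to evaluate stigmatization in patients with visible skin conditions". Under Study population, recruitment covers "all adult patients with chronic pruritus, regardless of the IFSI classification to skin manifestation", and non-inflamed skin is one of the classes listed there. Study III records IFSI class and itch localization for each patient.

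**The concern.** A known-groups test is informative only when theory says that the groups should differ on the construct. Itch severity meets that condition for the itch, disease-control and ItchyQoL scales. For PUSH-D, the protocol's own definition points to visibility instead. A patient with intense itch on normal-looking skin may report little stigma of the kind PUSH-D asks about, and a patient with mild itch and conspicuous lesions may report a great deal.

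The VAS comparison can therefore mislead in both directions. A sound scale may show little gradient because some patients lie outside its target population. A gradient may also appear only because severe itch tends to come with more visible lesions. Primary objective 1 is to establish validity for Thai patients with chronic pruritus, so a known-group result that is hard to interpret weakens the evidence for one of the three translated scales.

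**Working it through.** **The plan's own figure.** The article gives no effect size or power for the known-group comparison, so there is no figure to reproduce. The Sample size estimation section is used only for N: 396 × (1 − 0.20) = 316.8, about 317 patients with data.

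**Inputs from the article.** Four VAS bands, two-sided P < 0.05, N = 317, PUSH-D with 17 items.

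**Assumed inputs (not in the article).**
- Band shares of 20/50/20/10%.
- ρ, the latent correlation of PUSH-D with itch intensity among visibly affected patients: 0.1 to 0.4.
- q, the share of patients without visible lesions: 0 to 60%, independent of itch intensity.
- Scores of non-visible patients: either unrelated to itch (*unrelated*) or concentrated near the bottom of the scale (*floor*).

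**Method.** For visibly affected patients, score = ρ·z + √(1 − ρ²)·e, where z is latent itch intensity and e is independent standard normal noise. For non-visible patients the score is standard normal noise (*unrelated*) or normal with mean −1.5 and SD 0.3 (*floor*). Bands are cut from z. A Kruskal-Wallis test compares the four bands, with 400 runs per cell. The Monte Carlo standard error is at most √(0.25/400) = 0.025.

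Share of runs significant across VAS bands, N = 317:

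| ρ | Model | q = 0 | q = 20% | q = 40% | q = 60% |
|---|---|---|---|---|---|
| 0.1 | unrelated | 0.212 | 0.140 | 0.113 | 0.060 |
| 0.1 | floor | 0.217 | 0.185 | 0.122 | 0.070 |
| 0.2 | unrelated | 0.785 | 0.588 | 0.355 | 0.168 |
| 0.2 | floor | 0.785 | 0.465 | 0.228 | 0.085 |
| 0.3 | unrelated | 0.995 | 0.932 | 0.685 | 0.350 |
| 0.3 | floor | 0.988 | 0.835 | 0.472 | 0.200 |
| 0.4 | unrelated | 1.000 | 0.995 | 0.922 | 0.580 |
| 0.4 | floor | 1.000 | 0.980 | 0.762 | 0.273 |

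**Reading the table.**
- With ρ of 0.3 to 0.4 and q = 20%, the chance of a miss is small: 1 − 0.980 = 0.02 to 1 − 0.835 = 0.17 (floor).
- At q = 40% it is 0.24 to 0.53 (floor) or 0.08 to 0.32 (unrelated).
- At q = 60% it is 0.73 to 0.80 (floor) or 0.42 to 0.65 (unrelated).
- With ρ = 0.1, power is only about 0.21 even when every patient has visible lesions. The mismatch of construct then matters without any non-inflamed patients.
- With all 396 patients the pattern is the same: floor model, q = 40%, power 0.62 at ρ = 0.3 and 0.84 at ρ = 0.4.

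The simulation covers only a missed gradient. The opposite error, a gradient carried by lesions rather than stigma, follows from reasoning and is not quantified here.

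**Precision of a visible versus non-inflamed comparison.** The standard error of a standardised difference is √(1/n₁ + 1/n₂), and the 95% half-width is 1.96 times that.
- q = 20% (63 v 254): √(1/63 + 1/254) = 0.141, half-width 0.28 SD.
- q = 40% (127 v 190): 0.115, half-width 0.22 SD.
- q = 5% (16 v 301): 0.257, half-width 0.50 SD, so a rare non-inflamed class would make this comparison imprecise.

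**Patients per item in the visible subset.** 254/17 = 14.9, 190/17 = 11.2 and 127/17 = 7.5 at q = 20, 40 and 60%. All lie within the plan's 5–15 per item.

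**The case against.** *The scope is inferred.* The known-group sentence names no scale and does not say that it applies to all of them, and an article condenses a fuller protocol that may hold scale-specific hypotheses. This stands as a caution. But the article does state a criterion, with cut-points, in a paragraph about the whole set. The point concerns what is fixed there, not what is left out.

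*Nothing can formally fail.* A reader might infer that a sound Thai PUSH-D would be declared invalid. The article does not support that. It sets no pass mark for known-group validity, unlike α and ω or the fit indices. Known groups are one strand beside expert and patient content review, factor analysis, item response theory, convergent validity, reliability and patient interviews. This objection stands and limits the consequence to weak, ambiguous evidence.

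*Itch and stigma may be well correlated.* A reader might go further and suppose that the VAS test has almost no chance of significance. That requires stigma to be independent of itch, which assumes the answer. With a moderate correlation and about 20% non-visible, the VAS test performs well. Scratch lesions are visible, so only the non-inflamed class is affected.

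*TAS-20.* A reader might extend the argument to alexithymia. Table 2 gives TAS-20 no target population that conflicts with the cohort, and the article does not show that another collected measure would be a better known group. That extension is not made here.

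*The full cohort is the population of interest.* Primary objective 1 concerns chronic pruritus patients generally, so confining PUSH-D validation to visible disease would leave its behaviour in the rest unknown. This stands, and the fix respects it.

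**Conclusion.** The concern holds in a limited form. The only known-group criterion named does not match the construct that the article itself gives for PUSH-D, in a cohort that includes patients outside that construct's target. A flat or rising VAS gradient is therefore weak evidence against or for the Thai PUSH-D.

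The loss is small at about 20% non-visible if the stigma-itch correlation is 0.3 or more. It is substantial at 60%, and at 40% unless the correlation is about 0.4 and non-visible scores do not pile up at the floor. It is also substantial whenever the correlation is weak. Both quantities are assumptions, as are the band shares and the score models. The premises are firm, but the size is not known from the article.

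**What to change.** In the psychometric paragraph of the Statistical analysis plan:
- Keep the VAS bands as known groups for the itch, disease-control and ItchyQoL scales.
- For PUSH-D, prespecify visible skin changes (IFSI inflamed skin or chronic scratch lesions) versus non-inflamed skin as the main known-group comparison. State the expected direction, and report the difference with a confidence interval. Keep the VAS bands as supportive.
- Keep the full cohort as the primary validation sample, and report PUSH-D reliability and structure in visibly affected patients as a sensitivity analysis.

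IFSI class is already recorded, so no new data are needed. The cost is a little more analysis, and the comparison will be imprecise if few patients have non-inflamed skin. The Cohort status section reports 70 patients as of October 30, 2024, against a minimum of 396. At that stage the change could still be made before most of the data were in.
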